**Fig. 1 Fig1:**
[figure not shown]
Flow of participants through the study

Enrolled participants will access the registration page and enter demographic, clinical, and psychosocial information, and topics of interest selected from 18 predefined items (Supplementary Table 1). These items were developed based on the Zenganren × J-SUPPORT × SaQRA Research and Development Map [18].

Using Hibilog, an Interactive Web Response System (Accelight, Inc.), participants will be randomized using permuted block randomization to either the peer support group, which will immediately schedule a session, or the waitlist control group, which will schedule a session 2 weeks after registration. The block size will be confidential, with access limited to the system administrator. No stratification factors will be applied, given the small sample size in this pilot study. This randomized design with a waitlist group will enable us to simultaneously estimate intervention effects and examine satisfaction with the peer support session using data from both groups.

Participants will then attend peer support sessions and complete a suite of outcome measures described below. They may receive up to 4,000 Japanese yen (approximately 28 USD based on the exchange rate at the time of study planning) in Amazon gift cards based on completion of study questionnaires.

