### Peer support

Participants randomized to the peer support group will schedule a session immediately after registration, while those in the waitlist group will schedule their session 2 weeks later. Reminders will be sent as needed by the study coordinating team if no reservation is made. Appointments will be made via a web system, allowing participants to select preferred dates and times from slots pre-specified by peer supporters. Participants in the waitlist group will be instructed not to engage in other peer support activities during the waiting period.

Each participant will receive a single approximately 40-min online session via Zoom, a web-based video conferencing system (Zoom Video Communications, Inc.). The session will be conducted by two peer supporters. Peer supporters will be provided with a manual that describes the procedures and general guidance, and the outline is shown in Supplementary Table 2. A primary supporter will lead the session, and a secondary supporter will manage time, record the session, and request questionnaire completion at the end. The second supporter will reduce the burden on the primary supporter by handling these tasks and will enhance session quality by addressing participants’ questions that the primary supporter may not be able to answer adequately. Peer supporters will report any issues occurring during each session, including technical problems (e.g., connectivity issues), adherence to session duration, and other difficulties encountered during the session.

Peer supporters will be recruited by CancerNet Japan, a non-profit organization that provides evidence-based cancer information and has offered a training program for breast cancer survivors to become peer supporters since 2007 [19]. Most graduates of this course engage in patient group activities or peer support, and CancerNet Japan maintains a nationwide network.

The eligibility criteria for peer supporters are: (1) female breast cancer survivors; (2) completion of the training program developed by the Ministry of Health, Labour and Welfare [3]; and (3) prior peer support experience. Criteria (2) and (3) are intended to ensure session quality. The training program is designed for individuals interested in peer support and focuses on sharing personal experiences with others [3]. It also provides guidance on protecting privacy and maintaining appropriate boundaries, such as refraining from offering opinions or advice regarding diagnoses or treatment.

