### Statistical analyses

We will calculate effect sizes using mean differences and standard deviations, and compare UCLA Loneliness Scale scores between the peer support group at 1 week after the session and the waitlist group at the end of the 2-week waiting period. Comparisons will be performed using the Wilcoxon rank-sum test. A t-test will also be conducted when the score distributions approximate normality. The analysis will include all participants with available outcome data for comparison. The same analyses will be applied to other measures.

In addition, we will explore a linear regression model with participants’ satisfaction as the outcome. Explanatory variables will include participant characteristics, peer supporter characteristics, and similarity between participants and peer supporters (e.g., age difference, shared topics of interest). Data from all participants who complete satisfaction assessments after peer support will be included. This exploratory model will be refined, guided by the statistical significance of variables and the Akaike information criterion. Based on the final model, we will propose a potential approach for matching participants with peer supporters.

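### The satisfaction model pools both arms, but randomised arm is not named as a term or protected from variable selection; fixing it as a term is a cheap, minor improvement

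*Protocol article*

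**What the plan says.** Pooling is deliberate. The Procedure section gives it as one reason for the waitlist design, which is to let the investigators "examine satisfaction with the peer support session using data from both groups". Statistical analyses then sets the analysis population: "Data from all participants who complete satisfaction assessments after peer support will be included".

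The same section names three classes of candidate: "Explanatory variables will include participant characteristics, peer supporter characteristics, and similarity between participants and peer supporters". Neither randomised arm nor time from registration to session is among them. On selection it says: "This exploratory model will be refined, guided by the statistical significance of variables and the Akaike information criterion". No term is marked as always retained, and the final model is the basis of the proposed matching approach.

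The arms differ before the session. The control arm is "the waitlist control group, which will schedule a session 2 weeks after registration", and Table 1 gives it an additional assessment at the end of the wait. The supporter is reached after randomisation, through a web system "allowing participants to select preferred dates and times from slots pre-specified by peer supporters".

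**The concern.** Randomisation makes arm independent, in expectation, of the participants' baseline characteristics. It does not do so for supporter characteristics or similarity, which are settled later by slot booking. The waitlist arm books 2 weeks later, from whatever slots are then on offer.

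Two consequences follow if arm is left out. First, any effect of the wait (or of the extra questionnaires) on satisfaction becomes unexplained variation, which makes real factors harder to detect. Second, if a supporter trait were associated with arm, part of the wait effect would appear in that trait's coefficient. It could then influence which variables survive selection and so shape the matching proposal.

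Nor does any analysis described in the article compare satisfaction between arms. The comparison specified for loneliness, and extended to the other measures, sets the 1-week post-session score against the score at the end of the wait. Table 1 does not collect satisfaction at the end of the wait, so that comparison cannot be made for it.

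**Working it through.** **The plan's own figure.** The satisfaction model has no numerical sample-size basis. The 470 in Sample size calculation belongs to the loneliness comparison. It reproduces: d = 0.3, 90% power and two-sided 5% give 234.46 per arm by the noncentral t, so 235 per arm and 470 in total. Ten per cent of that is 47, and the planned 50 is 10.6%. This neither supports nor weakens the present point.

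**Inputs.** N = 50 is from the article. The allocation ratio is not stated, so 1:1 (25 per arm) is assumed. The article gives neither the satisfaction SD, nor an effect of the wait on satisfaction (d, in residual SD), nor a correlation between arm and a supporter factor (r). All are assumptions, shown over a range.

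**Residual variance.** A two-level term with equal arms has variance d²/4. Omitting it multiplies residual variance by 1 + d²/4 and standard errors by the square root of that.

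| d | d²/4 | Residual variance | Standard error |
|---|---|---|---|
| 0.3 | 0.0225 | +2.3% | +1.1% |
| 0.5 | 0.0625 | +6.3% | +3.1% |
| 0.8 | 0.16 | +16% | +7.7% |

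For one factor with a true standardised effect of 0.4 and r = 0, simulated power without and with arm is about 75% and 77% at d = 0.5, and about 72% and 76% at d = 0.8.

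**Leakage.** The expected shift in a standardised factor's coefficient is about (d/2) × r. For d = 0.5 and r = 0.3 this is 0.25 × 0.3 = 0.075 SD. Simulation of a null factor in a six-covariate model (N = 50, 8,000 runs per cell, arm omitted) gave:

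| r | d = 0.3: bias, false positives | d = 0.5 | d = 0.8 |
|---|---|---|---|
| 0 | 0.00, 5.2% | 0.00, 5.2% | 0.00, 5.1% |
| 0.3 | 0.05, 5.5% | 0.08, 7.6% | 0.12, 11.7% |
| 0.5 | 0.08, 7.7% | 0.13, 12.2% | 0.21, 23.4% |

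With arm in the model, bias is about zero and the false-positive rate is 4.4% to 5.4% in every cell.

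**How large might r be?** By chance alone its SD is about 1/√49 = 0.14. The typical shift is then 0.15 × 0.14 = 0.02 SD (d = 0.3) to 0.4 × 0.14 = 0.06 SD (d = 0.8), with mean zero, against a coefficient standard error of about 0.15 to 0.16.

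For a systematic link, suppose the supporter mix drifted from 25/75 to 75/25 over the study; this is purely illustrative. A 2-week lag moves the mix by about 50 × 2/(6 + 2) = 12.5 points with 6 weeks of recruitment, and 50 × 2/(26 + 2) = 3.6 points with 26 weeks. With equal arms and a mix near 50/50, r roughly equals that difference, so about 0.13 and 0.04. A separate simulation gave about 0.10 and 0.03. At r = 0.1 and d = 0.5, bias is 0.25 × 0.1 = 0.025 SD and the false-positive rate is about 5%.

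**Cost of the arm term when d = 0.** The mean standard error goes from 0.152 to 0.154 (+1%) at r = 0, from 0.1525 to 0.1617 (+6%) at r = 0.3, and from 0.1519 to 0.1783 (+17%) at r = 0.5.

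**Precision of an arm contrast.** With 25 per arm, the 95% half-width is t(0.975, 48 df) × √(2/25) = 2.01 × 0.283 = 0.57 SD.

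**The case against.** The strongest reply is that the article does not exclude arm. The list of explanatory variables is worded openly, the article condenses a fuller protocol, and exact covariates are often left to an analysis plan. This stands as far as it goes: the text supports saying that no arm term is named, not that the model has none. It does not answer the selection rule, which the article does state and which protects no term. Arm offered as an ordinary candidate could be dropped at N = 50.

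Second, a reader might infer that the matching rule will be biased. The documents do not support that. Bias needs both a real effect of the wait on satisfaction and a systematic difference in supporter factors by arm. Neither is shown, both arms use the same booking system, and no changing supporter pool is described. Chance links average to zero and do not raise the false-positive rate, and even the invented drift leaves it close to nominal.

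Third, a reader might infer that the plan gives up the between-arm estimate for satisfaction. It does not: satisfaction is collected after the session in both arms, so the contrast can be made whatever the regression contains. Nor could that contrast justify pooling, because a half-width of 0.57 SD cannot exclude the 0.3 or 0.5 SD effects considered here.

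Finally, the model is labelled exploratory, and the Discussion says larger datasets will be needed to refine it. That limits the consequences, but it gives no reason to leave a known design factor unprotected.

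**Conclusion.** The point holds as a minor improvement. The model pools two arms with different routes to the session, does not name arm, and exempts no term from selection. Any wait effect would then be left in the residual. On the assumed effects the loss is small: about 2 points of power at 0.5 SD and about 4 points at 0.8 SD.

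Material leakage into supporter or match coefficients is conditional. It needs at least a moderate wait effect together with an arm-factor correlation of around 0.3 or more, and the article gives no evidence of either. All sizes rest on assumed values of d and r and on 1:1 allocation. No conclusion about the effect on loneliness depends on this model.

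**What to change.** Add to Statistical analyses that randomised arm is a fixed term in every version of the satisfaction model and is not subject to selection by significance or AIC.

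Report the between-arm difference in satisfaction with its 95% interval from a model without supporter or similarity terms, since those arise after randomisation. Present it as description only and not as a test of whether pooling is justified. Note that only participants who attend a session and complete the questionnaire contribute.

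The change needs no new data, participants or procedures. It costs one parameter and a standard error about 1% larger for factors unrelated to arm, or about 6% larger at a correlation of 0.3. If the wait does not affect satisfaction, that small loss brings no gain.

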At study initiation, peer supporters will report their demographic and social characteristics, indicate topics they have experienced, and complete the Japanese version of the Posttraumatic Growth Inventory (PTGI-J) [20].

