### Sample size calculation

One aim of this pilot study is to estimate the effect size required for a future randomized controlled trial, since no reference value is available in this study design. Therefore, we estimated the sample size assuming an effect size (Cohen’s d) of 0.3. A two-sample t-test with this effect size, 90% power, and a two-sided significance level of 5% requires 470 participants. Based on a previous study [32], we set the sample size at approximately 10% of that number, i.e., 50 participants.

In addition, a sample size of approximately 50 participants is considered sufficient for a multivariable linear regression model examining factors related to satisfaction with peer support. From this perspective as well, we concluded that 50 participants represent an appropriate sample size.

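### Selecting the satisfaction model by p-values and AIC on at most 50 participants risks keeping noise factors and overstating fit, and the claim that about 50 is enough is tied to no number of predictors

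*Protocol article*

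**What the plan says.** Under Statistical analyses, the protocol article plans to regress satisfaction on three families of variables: "Explanatory variables will include participant characteristics, peer supporter characteristics, and similarity between participants and peer supporters (e.g., age difference, shared topics of interest"). On the analysis set it says: "Data from all participants who complete satisfaction assessments after peer support will be included". Both arms contribute, so n is at most 50. The selection rule is: "This exploratory model will be refined, guided by the statistical significance of variables and the Akaike information criterion". The use of the result follows: "Based on the final model, we will propose a potential approach for matching participants with peer supporters".

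Under Sample size calculation, as a second reason for the number 50, the article states that "a sample size of approximately 50 participants is considered sufficient for a multivariable linear regression model examining factors related to satisfaction with peer support". It gives no predictor count, R², power or precision target for this model.

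The data from which candidates could come are described elsewhere. Under Procedure, participants "enter demographic, clinical, and psychosocial information, and topics of interest selected from 18 predefined items". Under Peer support, "peer supporters will report their demographic and social characteristics, indicate topics they have experienced, and complete the Japanese version of the Posttraumatic Growth Inventory".

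The Discussion says that the confirmatory trial will incorporate the matching strategy. Among the limitations, it says that small numbers of participants and supporters restrict generalizability and that larger datasets will be needed to refine the model.

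**The concern.** Choosing variables by significance or AIC and then reading the chosen model on the same data has known effects. The p-values of the retained variables are no longer valid, their coefficients are too large on average, R² is too high, and the chosen set changes from sample to sample. The effects grow as the number of candidates rises relative to n. Here n is at most 50 and the pool of collected data is wide.

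Whether 50 is enough for a multivariable model depends on how many predictors are tried and how strong they are, so a sufficiency statement that names neither cannot be checked.

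What is at stake is the second aim. The factors that survive selection shape the matching approach, and the confirmatory trial is meant to use it. A factor retained by chance could be built into that trial's intervention.

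**Working it through.** **1. The plan's own figure.** For the two-sample comparison with d = 0.3, 90% power and two-sided 5%, the normal approximation gives 2(1.960 + 1.282)²/0.3² = 233.5, so 234 per arm and 468 in total. The exact t-test solution is 234.46, so 235 per arm and 470 in total, as stated. Ten percent of 470 is 47, and 50/470 = 10.6%, consistent with roughly 10%. The regression statement has no inputs, so there is nothing to reproduce.

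**2. Inputs for the check.** From the document: n = 50 at most, and selection by significance and AIC. Assumed, because not stated: k = 5, 10 or 20 candidates; a 0.05 threshold for significance; backward elimination; independent standard normal predictors; no missing satisfaction data; independent observations.

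On the plausible size of k, the baseline scores alone are UCLA (1), GAD-7 (1), PHQ-9 (1), CARS-J (1), SCNS domains (5) and mDAMS scores (3). That is 12 before any QLQ-C30 scale, demographic, clinical, supporter or similarity variable. These are data collected, not a stated candidate list.

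**3. Closed-form approximation, no true factor.** P(at least one noise factor) ≈ 1 − (1 − α)^k. AIC keeps a single variable when its likelihood-ratio statistic exceeds 2, which corresponds asymptotically to α = P(χ²₁ > 2) = 0.157.

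- k = 5: 1 − 0.95⁵ = 0.23; 1 − 0.843⁵ = 0.58
- k = 10: 0.40; 0.82
- k = 20: 0.64; 0.97

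**4. Simulation of backward elimination, n = 50, no true factor.**

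| k | P(≥1 noise), p < 0.05 | P(≥1 noise), AIC | Mean noise factors kept, AIC | Apparent R², AIC | New-data R², AIC |
|---|---|---|---|---|---|
| 5 | 24% | 62% | 0.9 | 0.06 | -0.08 |
| 10 | 39-44% | 86% | 2.1 | 0.13 | -0.18 |
| 20 | about 70% | 98% | 5.5 | 0.30 | -0.49 |

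The simulated chances lie close to the closed form, mostly a little above it. A negative new-data R² means that the model predicts worse than the overall mean.

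**5. Simulation with three true factors.**

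- Partial r about 0.3, k = 20: each true factor is kept in about 53% (p < 0.05) or 74% (AIC) of runs. The noise share of selected factors is roughly 41-47% or 65-68%; the spread reflects averaging the share over runs versus pooling all selected factors. New-data R² is -0.08 or -0.23.
- Partial r about 0.3, k = 5: the noise share is about 5% or 12%, and new-data R² is +0.07 or +0.10.
- Partial r 0.5, k = 20: true factors are kept in 95% or 98% of runs, and new-data R² is +0.35 or +0.24.

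**6. What 50 can support.** Consider the t-test of one coefficient with partial correlation r among k predictors. With noncentrality r/√(1 − r²) × √(50 − k) and 50 − k − 1 degrees of freedom, power at two-sided 5% is:

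- r = 0.3: 54% (k = 5), 49% (k = 10), 38% (k = 20)
- r = 0.5: 97%, 95%, 86%

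So 50 may be ample or inadequate, depending on two quantities that the article does not state.

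**The case against.** The strongest defence has four parts.

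**The number of candidates is unknown.** The article names three families and two examples. The 18 topics could enter as one count of shared topics, and the final list may be short. This stands, and every figure above is conditional on k.

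**The procedure is not automated AIC.** Refinement is guided by both criteria, and a significance rule is stricter. This also stands: with 5 candidates and p < 0.05, the null chance of keeping any noise factor is 24%, and an empty model remains possible.

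**The article is candid.** It calls the model exploratory and the output a potential approach, and it says that larger datasets are needed. This lowers the stakes. However, the limitation is put as one of generalizability, whereas selection bias arises within the sample itself. The matching strategy is still carried into the confirmatory trial.

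**Validation and shrinkage may be described in the full protocol or analysis plan.** They may be, and the article's silence on them is not the point. The point rests on two things the article does state: the selection rule and the unqualified sufficiency claim.

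A reader might infer that the procedure will almost surely return noise as the matching rule. The document does not support that. A chance of 95% or more requires AIC selection, about 15 or more candidates and no true factor, all together. Keeping some noise factors is also not the same as the rule being only noise, because real factors are partly retained at partial r about 0.3 and nearly always at 0.5.

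**Conclusion.** The concern holds in conditional form, as a should-fix. The stated selection rule, applied to at most 50 participants, carries a material risk of retaining noise factors and overstating fit. Under no true factor that risk runs from about 24% (p < 0.05) to 62% (AIC) with 5 candidates, and from about 70% to 98% with 20. With 20 candidates and moderate true factors, roughly two fifths to two thirds of the selected factors are noise and prediction in new data is no better than the mean. With few candidates or strong factors, the model keeps real signal.

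The claim that about 50 is enough has no stated basis, because it names no number of predictors.

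The figures rest on independent normal predictors, backward elimination, complete satisfaction data and independent observations. The number of supporters is not given. If the same supporters serve many participants, there is less information on supporter characteristics than these figures assume.

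**What to change.** - In place of selection by p-values and AIC, fit a short candidate set listed before the data are reviewed, with similarity measures first and shared topics as one count. Alternatively, fit all candidates by penalised regression (ridge or lasso).
- Bootstrap the whole procedure, including any selection or tuning. Report selection frequencies and optimism-corrected R² beside the proposed matching approach.
- Under Sample size calculation, restate that about 50 participants support only a small, stated number of predictors, and call the result hypothesis-generating.

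A cap of five predictors, or proposing a matching approach only if corrected R² exceeds zero, are options rather than requirements.

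The cost is revised analysis wording and a bootstrap on data already planned; recruitment, sample size and data collection do not change. The downside is fewer factors reported as significant and a less favourable R².

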Therefore, optimized matching may enhance the effectiveness of online peer support. This approach may complement existing medical resources and help reduce regional disparities in Japan, where psycho-oncology specialists are scarce [12], and may also enhance peer supporters’ self-efficacy through engagement. This pilot randomized controlled trial (Helping each Other by Peer Empowerment for Breast Cancer [HOPE-BC]) aims to generate preliminary data on effect sizes, particularly regarding loneliness outcomes, for future research. A second aim is to examine factors influencing participants’ satisfaction with peer support to help develop a matching algorithm for use in future research.

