## Discussion

This pilot randomized controlled trial is designed to preliminarily explore the effect of online peer support for individuals with early-stage breast cancer. We will calculate effect sizes for each outcome and conduct preliminary analyses to develop a matching algorithm. We will then generate evidence for online peer support through a confirmatory trial that incorporates the matching strategy. Such an approach may provide psychosocial support without using medical resources and help address regional disparities in cancer care in Japan [12].

The strengths of this study will include the following. First, to our knowledge, no prior study has examined peer supporter matching for breast cancer survivors, and the findings will be novel. Second, the randomized design with the waitlist control group will enable us to simultaneously estimate intervention effects and explore a matching algorithm, even with a relatively small sample size. Third, the study will apply a DCT system [13–17], which will reduce the burden on both participants and clinicians substantially. Fourth, peer supporters will have prior experience and will have completed training provided by the Ministry of Health, Labour and Welfare [3]. While interventions by untrained peer supporters sometimes have adverse effects [5], such risk will be low in this study.

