Nevertheless, several limitations should be noted. First, the intervention will include a single session, which may result in an insufficient effect size to achieve adequate statistical power. In addition, the effects of multiple sessions cannot be assessed in this trial. Future research may need to recruit a larger number of participants and examine the effectiveness of multiple sessions. Second, participants may receive informal support through social media or interactions at their medical institutions, which cannot be fully controlled or evaluated in this study. Third, although participants in the waitlist group will be instructed not to receive peer support outside the study during the waiting period, this protocol does not include procedures to monitor adherence to this instruction. In addition, psychosocial support outside the study will not be restricted due to ethical considerations. Therefore, monitoring and sensitivity analyses accounting for external exposure will be necessary in future studies. Fourth, while this protocol includes procedures to ensure and enhance the quality of peer support sessions, no quantitative scales to evaluate these aspects are included, which will need to be considered in future studies. Fifth, outcomes will be assessed 1 week after the session, and longer-term effects will remain unexplored. Sixth, given the many psychological measures collected, group differences may appear due to multiple testing. Thus, findings will need to be interpreted with caution. Finally, although this pilot study will provide insights into factors for matching, the small number of participants and peer supporters will limit the generalizability of these findings. Larger datasets will ultimately be required for model refinement. Taking these limitations into account, we will design subsequent confirmatory trials.

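### The plan commits to a matching approach from whatever regression model survives selection, but a model left with only participant and supporter main effects cannot say who should be paired with whom

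*Protocol article*

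**What the plan says.** The Introduction gives the purpose: "A second aim is to examine factors influencing participants’ satisfaction with peer support to help develop a matching algorithm for use in future research". The Statistical analyses section says how this will be done. First, "we will explore a linear regression model with participants’ satisfaction as the outcome". Next come the candidates: "Explanatory variables will include participant characteristics, peer supporter characteristics, and similarity between participants and peer supporters", with age difference and shared topics as examples of similarity. Then the reduction rule: "This exploratory model will be refined, guided by the statistical significance of variables and the Akaike information criterion". Last, the output: "Based on the final model, we will propose a potential approach for matching participants with peer supporters".

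The Discussion looks ahead: "We will then generate evidence for online peer support through a confirmatory trial that incorporates the matching strategy". It also limits the claim, noting the small numbers of participants and supporters and adding "Larger datasets will ultimately be required for model refinement".

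The text does not say that any similarity term is kept through selection, and it attaches no condition to the step from final model to matching approach.

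**The concern.** The three families of variables answer different questions. A participant characteristic predicts who tends to be satisfied, and its contribution is the same whichever supporter she meets. A supporter characteristic predicts who tends to give satisfying sessions, and it ranks supporters identically for every participant. Only a term that depends on both members of the pair bears on who should meet whom.

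The plan treats the three families alike during selection and derives the matching approach from whatever remains. Two outcomes are then open. The pairing terms may all be dropped, so that the promised approach rests on a model that is silent about pairing. Or a pairing term may survive by chance and be carried forward as a matching factor. Matching is the second stated aim and the ingredient that the confirmatory trial is meant to add, so the distinction matters for what the pilot hands on.

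**Working it through.** **The plan's own figure.** A two-sample t-test with d = 0.3, 90% power and two-sided 5% gives 235 per arm by the noncentral t distribution, 2 × 235 = 470 in total, as stated (the normal approximation gives 2 × 234 = 468). Ten percent of 470 is 47, rounded up to 50. The point below uses only the resulting n of about 50.

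**Step 1: what a main-effects model can say.** Let predicted satisfaction for participant *i* with supporter *j* be aᵢ + bⱼ. For any one-to-one assignment π, the total is

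Σ(aᵢ + b_π(i)) = Σaᵢ + Σbⱼ,

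which does not depend on π. Numerically, with 12 participants and 12 supporters, 1000 random pairings gave totals that differed by about 2 × 10⁻¹⁵, that is, zero. After adding a penalty on absolute age difference, the best pairing totalled 0.82 against a random mean of −3.75. If supporters may take unequal numbers of sessions, the additive model can favour some supporters, but the same ones for everyone. That is selection of supporters, not matching.

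**Step 2: which terms carry pairing information.** Absolute age difference, the number of shared topics and participant-by-supporter interactions do. A signed age difference entered linearly does not: c(Aᵢ − Sⱼ) = cAᵢ − cSⱼ is again a sum of main effects. A label of similarity is therefore not enough.

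**Step 3: how often selection removes every similarity term.** The article gives no number of candidates and no effect sizes, so these inputs are assumptions: n = 50; independent standard-normal covariates; one participant and one supporter effect of 0.3 residual SD per SD; similarity effect 0 or 0.3; backward elimination; 1500 runs per setting. A term is dropped if n·ln(1 + t²/df) < 2 (AIC) or if p > 0.05.

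| Candidates (participant + supporter + similarity) | True similarity effect | No similarity term kept, AIC | No similarity term kept, p < 0.05 |
|---|---|---|---|
| 4 + 3 + 2 = 9 | 0 | 61% | 88% |
| 6 + 4 + 3 = 13 | 0 | 47% | 80% |
| 8 + 5 + 5 = 18 | 0 | 23% | 69% |
| 9 | 0.3 | 21% | 44% |
| 13 | 0.3 | 15% | 42% |
| 18 | 0.3 | 8% | 33% |

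The complements of the no-effect rows are the chance of keeping at least one spurious similarity term: 39% to 77% under AIC and 12% to 31% under p < 0.05.

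A second set of assumptions (5 + 3 + 3 = 11 candidates, main effects explaining 15% of variance, 3000 runs) agrees. The share with no similarity term was 49% (AIC) and 82% (p < 0.05) with no pairing effect, 24% and 53% when similarity explained 5% of variance, and 10% and 30% when it explained 10%.

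**Step 4: what a joint test can do at this size.** With the same 11 candidates and a true similarity effect of 5% of variance, a joint F test of the three similarity terms was significant in only about 21% of runs.

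**The case against.** The strongest reply is that the work is openly exploratory. The article speaks of a potential approach, wants only to help develop an algorithm, and concedes that larger datasets are needed. Participant and supporter variables may be in the model simply to adjust the similarity terms, which is good practice. The fuller protocol, not shown, may say what happens if no similarity term survives. The sentence about the confirmatory trial is a statement of intent in a Discussion, not an analysis rule. And the simulated percentages depend on assumed inputs: real similarity terms are built from participant and supporter values, supporters are few, and refinement is only guided by significance and AIC.

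Much of this stands. The percentages show that the outcome is plausible and do not predict its frequency. The hedging, however, concerns precision and generalizability. It does not make a main-effects model informative about pairing, and the published step from final model to matching approach is stated without condition.

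Two stronger readings are tempting and are not supported. A reader might infer that the trial has no way to report an absence of matching signal. But similarity variables are named candidates, they will be estimated, and nothing forbids reporting that none was retained. A reader might also infer that every surviving factor will enter the matching score. The text says only that the approach is based on the final model.

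A test that permutes pairings would not settle the matter either. Participants choose among supporters' slots and two supporters attend each session (Peer support section), so exchangeability of pairings is doubtful.

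**Conclusion.** The point holds in limited form. The stated procedure can lead from a model with no pairing information to a proposed matching approach, and it gives pairing terms no protection in selection. That a main-effects model cannot rank pairings is algebra and needs no assumption. That selection can easily drop all similarity terms, or keep one by chance, at about 50 participants rests on the assumed numbers of candidates, independent covariates and effect sizes. Across those tried, the no-effect share with no similarity term ran from 23% to 88%, depending on the criterion.

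The same calculations limit what a negative result could mean. A true effect of 0.3 SD per SD was missed in 8% to 44% of runs, so dropping the similarity terms would support only that no matching signal was found in this pilot, not that matching has no effect. This is an improvement worth making to the second aim. It does not affect the randomized comparison of loneliness.

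**What to change.** In the Statistical analyses section:

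- Name a small set of pairing terms in advance (absolute age difference, shared topics, any participant-by-supporter interaction of interest) and keep them in the model regardless of significance or AIC. Report each with a confidence interval, and all of them with one joint test.
- Use participant and supporter main effects as adjustment, and report them separately as case-mix and supporter differences.
- Build any proposed matching approach from the pairing terms only. If they show no signal, report that no matching signal was found in this pilot, without concluding that matching has no effect.

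In the Discussion, word the matching component of the confirmatory trial as depending on these results.

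The cost is a change of wording, with no new data. The downside is that the pilot may report no basis for an algorithm. Because the joint test has little power at n = 50 (about 21% in the case computed), it should inform the proposal alongside the intervals and not act as a hard gate.
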